### Data management

An electronic entry database will be established based on the CRFs project, and the outcome assessors will fill in relevant information in a timely and accurate manner according to the requirements of CRFs. Only outcome assessors have access to the CRFs and perform double-data entry. The Evidence-based Medicine Center of the Hospital of Chengdu University of TCM will be responsible for monitoring the study and data every 3 months.

### Data analysis

#### Clinical data analysis

The comprehensive effectiveness analysis will use the per protocol set (PPS) and the full analysis set (FAS). The FAS population will be used as the primary population for all efficacy analyses. The safety set (SS) included all subjects who received at least one treatment after randomization. When the results of PPS analysis and FAS analysis are inconsistent, PPS and FAS are discussed separately to find out the reasons for the inconsistency. Missing data will be handled using the last-observation-carried-forward (LOCF) method.

Statistical analysis will be conducted using SPSS 26.0 (IBM, Chicago, IL, USA) statistical software. *P* < 0.05 (two-sided) is considered statistically significant. Quantitative data are described with mean ± standard deviation (SD). Qualitative data are described with frequency and percentage (*N*, %). Student’s *t-*test and chi-square test will be used to compare the differences between groups at baseline. The assessment of the difference between the two groups will use repeated measures analysis of covariance (ANCOVA), taking into account the baseline values of age, sex and disease duration as covariates. Clinical data on skewed distribution will be compared using a non-parametric test.

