**Clinical assessment**										
VAS	√	√						√	√	√
NDI		√						√	√	√
ROM	√	√						√	√	√
PPT		√						√	√	√
SF-36		√						√	√	√
MSUS		√						√		
SAS and SDS		√						√	√	√
MRI (*n*=40)		√						√		
Laboratory test		√						√		
Adverse event								√		

This is a randomized controlled trial of neuroimaging including a 2-week baseline period, a 2-week treatment period, and a 12-week follow-up period. At baseline, patients will be screened based on inclusion and exclusion criteria; eligible individuals will then sign informed consent and undergo a physical examination. After being randomized into 2 groups, 6 acupuncture treatments will be performed for 2 weeks. Clinical data will be evaluated at baseline, after treatment ends, and at 4 and 12 weeks after completion; MRI scans will be performed at baseline and after treatment. After the treatment, laboratory tests will be performed, including routine blood test, C-reactive protein, and erythrocyte sedimentation tests. Adverse events will be recorded in the CRF at any time during treatment. Abbreviations:MRI magnetic resonance imaging, VAS visual analogue scale, NDI neck disability index, ROM range of motion, PPT pressure pain thresholds, MSUS musculoskeletal ultrasound, SF-36 Short-Form 36-Item Health Survey, SAS Self-rating Anxiety Scale, SDS Self-rating Depression Scale, CRF case report form

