#### Sample size

This study aims to compare the difference of the clinical efficacy of two acupuncture prescriptions (group A and group B). According to the results of the pilot study, the average reduction of VAS score in group A was 2.86±0.99, and the average reduction of VAS score in group B was 2.14±0.99. According to the formula, $$ n=\frac{2{\sigma}^2}{{\left(\mu 1-\mu 2\right)}^2}\times {\left({\mu}_{\alpha /2}+{\mu}_{\beta}\right)}^2 $$, with *α* = 0.05 (both sides) and 1 − *β* = 0.80 [24]. The sample size of each group was calculated to be 34, considering a 20% dropout rate; the final sample size was set to 43 per group, making the total of 86 in this study.

There is no widely accepted method for sample size calculation in neuroimaging study. Referring to the previous study [25], 15 participants in each group are the smallest size in neuroimaging studies. Considering a 20% dropout rate and the unavailability of data due to various reasons, this study will randomly select 20 patients from each group for MRI scans.

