### Outcomes

The measurements will be conducted by independent assessors who have been trained before the study. The primary outcome is the change of VAS scores at baseline and after the end of treatment. VAS scores range from 0 to 10, with 0 indicating no pain and 10 indicating pain is unbearable. The secondary outcome measurements include neck disability index (NDI), Short-Form 36-Item Health Survey (SF-36), Self-rating Anxiety Scale (SAS), Self-rating Depression Scale (SDS), range of motion (ROM), and pressure pain threshold (PPT) will be evaluated at baseline, after treatment, and at 4 and 12 weeks after the end of treatment. In addition, we will perform musculoskeletal ultrasound (MSUS) before and after treatment. Among them, NDI is the most widely used clinical tool for self-assessment of disability caused by NP [27]. The SAS and SDS are the commonly used psychometric tools to measure the severity of anxiety and depression [28, 29]. SF-36 is a general health-based survey of quality of life, which can be self-administered by the patient with reliability [30]. ROM is one of the quantitative outcomes assessing the extent and degree of joint motor impairment. The changes of the tenderness threshold can quantitatively reflect the improvement of the pain severity [31]. Meanwhile, MSUS is an important method for clinical diagnosis of rehabilitation medicine, tracking disease progression and assessing curative effect [32].

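### LOCF on the primary endpoint is baseline carried forward: early dropouts kept in the FAS score zero change, which conflicts with the sample size and can cost power

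*Protocol article*

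**What the plan says.** The section on clinical data analysis sets one rule for incomplete data: "Missing data will be handled using the last-observation-carried-forward (LOCF) method". The same section says "The FAS population will be used as the primary population for all efficacy analyses". It does not say whether a patient with no post-baseline VAS belongs to the FAS. The planned group comparison is a repeated measures ANCOVA with age, sex and disease duration as covariates, and a non-parametric test for skewed data. A per-protocol analysis is also planned, and any disagreement with the FAS result is to be examined.

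The Outcomes section defines the endpoint: "The primary outcome is the change of VAS scores at baseline and after the end of treatment". The note to Table 1 gives the timing: "Clinical data will be evaluated at baseline, after treatment ends, and at 4 and 12 weeks after completion". In the table itself, VAS is marked at weeks 0 and 2 (both baseline), 4 (end of treatment), 8 and 16. None is marked during treatment.

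The Sample size section takes its inputs from a pilot: "the average reduction of VAS score in group A was 2.86±0.99" and "the average reduction of VAS score in group B was 2.14±0.99". It uses a two-sided alpha of 0.05 and 80% power, arrives at 34 per group, and then, "considering a 20% dropout rate; the final sample size was set to 43 per group".

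**The concern.** LOCF needs an earlier value from the treatment period if it is to carry anything about response. Here there is none. For a patient who leaves before week 4, the last observation is the baseline VAS, so the imputed change is 0. That lies more than two SDs below the expected mean reduction in either arm (2.14/0.99 = 2.2; 2.86/0.99 = 2.9).

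The sample size treats the same patients differently. Raising 34 to 43 is right if dropouts contribute no outcome. If they return to the FAS as zeros, the group difference shrinks and the variance grows, and the allowance for dropout no longer protects power.

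Three further consequences follow.

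- For patients lost after week 4, LOCF holds the week-4 score fixed at weeks 8 and 16, although the Background describes neck pain as prone to return.
- Imputed values are analysed as if they had been observed.
- If early loss differs between arms, LOCF itself can create a group difference.

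**Working it through.** **Inputs.** From the Sample size section: mean reductions 2.86 (A) and 2.14 (B), SD 0.99 in each, difference 0.72, two-sided alpha 0.05, power 0.80, 34 per group before and 43 after the dropout allowance. From Table 1: no VAS between weeks 2 and 4. Assumed, because the article is silent: the share d lost before the week-4 VAS, equal in both arms and unrelated to response.

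**Step 1: the plan's own figure.** n = 2 × 0.99² × (1.96 + 0.842)² / 0.72² = 29.7, so 30 per group. The stated 34 does not reproduce at 80% power; it corresponds to 85%. This departure is conservative, and it is already contained in the results below, which use n = 43. The dropout step does reproduce: 34/(1 − 0.20) = 42.5, so 43.

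**Step 2: the endpoint under LOCF.** If early dropouts stay in the FAS, each patient's change is 0 with probability d and otherwise normal with mean μ and SD 0.99. Then:

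- expected difference = (1 − d) × 0.72
- variance in an arm = (1 − d) × 0.99² + d(1 − d) × μ²

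At d = 0.20:

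- difference = 0.8 × 0.72 = 0.576
- variance A = 0.8 × 0.980 + 0.16 × 8.180 = 2.093 (SD 1.447)
- variance B = 0.8 × 0.980 + 0.16 × 4.580 = 1.517 (SD 1.232)
- pooled SD = √((2.093 + 1.517)/2) = 1.343
- standard error = 1.343 × √(2/43) = 0.290
- ratio = 0.576/0.290 = 1.99

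A ratio that close to the critical value means power of about one half.

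**Step 3: power by share lost before week 4.** n = 43 per group, two-sided t-test on change, noncentral t. Simulation agrees within about 1 percentage point.

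| Lost before week 4 | Difference | Pooled SD | Power |
|---|---|---|---|
| 0% | 0.720 | 0.990 | 92% |
| 3% | 0.698 | 1.066 | 85% |
| 5% | 0.684 | 1.111 | about 80% |
| 10% | 0.648 | 1.207 | 69% |
| 15% | 0.612 | 1.283 | 59% |
| 20% | 0.576 | 1.343 | 50% |

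In the 20% row, about 86 per group would be needed to restore 80% power.

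**Step 4: the other reading of the FAS.** If patients without a post-baseline VAS are excluded, a 20% early loss leaves about 34 per group with difference 0.72 and SD 0.99. Power is then 84%, and the week-4 analysis is a completer analysis.

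**Step 5: false positives.** Suppose both arms truly improve by 2.5 points (assumed) and early dropout is 15% v 25% (assumed). The LOCF means are 0.85 × 2.5 = 2.125 and 0.75 × 2.5 = 1.875, a spurious difference of 0.25. The simulated rejection rate is about 14%. With 20% lost in both arms under the same null it is about 5%.

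**The case against.** A reader might infer that the trial has only 50% power at its planned dropout. The documents do not support that. The 20% is given without timing, and the study runs for 2 weeks of treatment and 12 weeks of follow-up. Patients lost after week 4 do not affect the primary endpoint. If losses were spread evenly over those 14 weeks (an assumption), 20% × 2/14 = 2.9% would be early and power would be about 85%, above target. What remains is that the protocol applies the 20% to the calculation for this endpoint, so heavy early loss is within its own planning.

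The FAS may exclude patients without a post-baseline VAS. A condensed article can leave that definition to the full protocol, so the missing definition is no fault in itself. On that reading zero-change scoring does not arise at week 4. The completer analysis and the frozen follow-up scores remain.

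The t-test is not the planned analysis. That is correct, but the difference is small. Averaging the three post-baseline visits, with a constant effect and within-patient correlation of 0.5 to 0.9 (both assumed), gives 51% to 56% at 20% early loss, because those patients are carried as zero at every visit. A rank test gives about 55% with 9 dropouts per arm.

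A reader might also infer that LOCF inflates the type I error here. It does so only if early dropout is unequal, and nothing in the article points to that: patients are blinded, and both arms have the same number of points, sessions and stimulation. The 14% is an illustration.

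The per-protocol analysis is a partial check. It can reveal a discrepancy, but the FAS stays primary and the check does not replace a sound missing-data method.

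**Conclusion.** The concern holds in a conditional form. LOCF is a poor primary rule for this visit schedule, because on the primary endpoint it can only carry baseline forward. For patients kept in the FAS it also contradicts the dropout allowance in the sample size.

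The cost in power ranges from none against the 80% target (early loss up to about 5%) to about 30 points (all 20% lost before week 4). That range rests on equal dropout between arms, loss unrelated to response, a t-test standing in for the repeated measures ANCOVA, and an FAS that keeps patients without a post-baseline VAS. If the FAS excludes them, there is no shortfall in power at week 4. What is left is a completer analysis at week 4, frozen scores at weeks 8 and 16, and imputed values treated as observed.

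This should be fixed. Confidence is high in the mechanism and medium in the size of the power loss.

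**What to change.** Replace LOCF as the primary method by one of the following:

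- multiple imputation by arm, using baseline VAS, NDI, age, sex and disease duration;
- a likelihood-based mixed model in which baseline VAS is one of the repeated outcomes, with group, visit and their interaction plus the planned covariates.

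The placing of baseline VAS matters. If it enters only as a covariate, a patient lost before week 4 has no outcome row and drops out of the model, so the analysis would not include all randomised patients.

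Add one delta-adjusted sensitivity analysis in which dropouts are assumed to do worse than the model predicts. Keep LOCF at most as a sensitivity analysis. State in the same place whether patients without a post-baseline VAS belong to the FAS, so that the dropout allowance and the analysis agree.

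The cost is a change of analysis wording and a little more analysis work. Both methods are available in SPSS 26, and no extra patients, visits or data are needed. The change should be made before unblinding.

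### The between-group test is not tied to the end-of-treatment VAS change that defines the primary outcome, does not name baseline VAS as a covariate, and gives way to a non-parametric test if data are skewed

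*Protocol article*

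**What the plan says.** The Outcomes section of the protocol article sets a single primary quantity: "The primary outcome is the change of VAS scores at baseline and after the end of treatment". The Sample size section plans a two-group comparison of mean VAS reduction: "the average reduction of VAS score in group A was 2.86±0.99" and "the average reduction of VAS score in group B was 2.14±0.99". It does not date that reduction; end of treatment is the natural reading given the Outcomes section.

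Table 1 schedules VAS at baseline, at end of treatment, and 4 and 12 weeks after treatment.

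Under Clinical data analysis, one general sentence covers the group comparison: "The assessment of the difference between the two groups will use repeated measures analysis of covariance (ANCOVA". The covariates listed are age, sex and disease duration. The next sentence adds: "Clinical data on skewed distribution will be compared using a non-parametric test". The section does not say which visits enter the model, which term or contrast decides, whether baseline is a level of time, or how skewness will be judged.

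**The concern.** A repeated-measures ANCOVA yields at least two group-related tests: a group main effect averaged over visits and a group-by-time interaction. With more than two time levels, neither is the end-of-treatment contrast. The main effect mixes in 12 weeks without study treatment, and the interaction asks whether the two profiles differ in any way. If the difference fades after the two-week course, an averaged test can miss an end-of-treatment difference of the size the trial was planned to detect. With the deciding term open, the choice could also be made after the results are seen.

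Two further features of the same paragraph affect the primary test. Baseline VAS is collected but is not a named covariate, although it is usually the strongest predictor of later VAS. And the switch to a non-parametric test makes the choice of primary analysis depend on the observed data, with no criterion. A standard rank test would also lose the covariate adjustment and the difference in VAS points.

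**Working it through.** **Inputs from the Sample size section.** Difference 2.86 − 2.14 = 0.72; SD 0.99; "0.05 (both sides) and 1 − *β* = 0.80"; 34 evaluable per group; "considering a 20% dropout rate; the final sample size was set to 43 per group".

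**Assumed, because the article does not give them.** The effect at the two follow-up visits; the correlation r between the changes at the three post-baseline visits (0.5 to 0.8, each change with SD 0.99); the correlation ρ between baseline and end-of-treatment VAS (0.3 to 0.7).

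**Step 1. The plan's own figure.** n = 2 × 0.99² / 0.72² × (1.960 + 0.842)² = 29.7, so 30 per group, against the stated 34. At 85% power the formula gives 33.9, so 34. The dropout step is right: 34 / 0.8 = 42.5, so 43. The difference is conservative and is a separate matter; 34 per group is used below. Powers are t-based.

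**Step 2. End-of-treatment change alone.** Standard error = 0.99 × √(2/34) = 0.240; 0.72 / 0.240 = 3.00; power 84% (92% at 43 per group). If only baseline and end of treatment are time levels, the group-by-time test is this same comparison, apart from covariates.

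**Step 3. Group main effect over the three post-baseline changes.** SD of the mean = 0.99 × √((1 + 2r)/3), which is 0.808, 0.848 and 0.922 for r = 0.5, 0.6 and 0.8.

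| Effect at end of treatment, +4 and +12 weeks | Mean | Power, r = 0.5 | r = 0.6 | r = 0.8 |
|---|---|---|---|---|
| 0.72, 0.72, 0.72 | 0.72 | 95% | 93% | 89% |
| 0.72, 0.54, 0.36 | 0.54 | 78% | 74% | 66% |
| 0.72, 0.36, 0 | 0.36 | 44% | 41% | 36% |

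**Step 4. Baseline VAS as a covariate at end of treatment.** With equal variances at the two visits, the raw SD is 0.99 / √(2(1 − ρ)) and the residual SD is that times √(1 − ρ²), which simplifies to 0.99 × √((1 + ρ)/2). This is 0.798, 0.857 and 0.913 for ρ = 0.3, 0.5 and 0.7. Power for 0.72 at 34 per group is 96%, 93% and 89%, against 84% for the unadjusted change.

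**The case against.** A reader might infer that the protocol tests the wrong effect: that the model runs over all four visits and the averaged group effect decides. The text does not say so. It lists no visits, and the Outcomes section defines the primary outcome by two time points only, with the follow-up visits attached in its prose to the secondary measures. On the two-time-point reading with the interaction deciding, the test matches the primary outcome and nothing is diluted. A contrast at end of treatment taken from a longer model would match too.

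The size of any loss is also uncertain. The documents give no follow-up effects or correlations, and a sustained effect makes averaging over post-baseline visits more powerful, not less. Far lower power, 16% to 29%, can be produced, but only by stacking three assumptions: baseline as a level of time, the group main effect as the deciding test, and complete fading. No passage supports that combination. In addition, the full analysis set is primary with last observation carried forward, so up to 43 per group may be analysed. The milder fading pattern then has 77% to 87% power and full fading 43% to 53%, against 92% for the single contrast.

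The article is condensed, and a separate analysis plan may name the contrast. Nor does it say that the non-parametric test would be unadjusted; adjusted rank methods exist.

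These points stand as limits on the size of the harm. They do not remove the defect in what is written: the article names a test, does not connect it to the primary outcome, gives a covariate list without baseline VAS, and lets the observed distribution change the method.

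**Conclusion.** The point holds as a loose link between primary outcome and primary test, of moderate severity. It does not hold as a finding that the trial tests a different effect or is underpowered for its primary question.

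Under readings the wording permits, power at 34 per group for a true end-of-treatment difference of 0.72 is 84% for the matching test. For a main effect averaged over the three post-baseline visits it runs from 36% (full fading, r = 0.8) to 95% (sustained effect, r = 0.5). These figures rest on the protocol's SD of 0.99, on the pilot reduction having been measured at end of treatment, and on assumed follow-up effects and correlations. The gain from naming one contrast adjusted for baseline VAS, about 89% to 96% power against 84%, needs only the assumed pre-post correlation of 0.7 to 0.3 and equal variances at the two visits.

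**What to change.** State in Clinical data analysis that:

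- the primary test is the adjusted A-B difference in VAS at end of treatment, with 95% CI, from an ANCOVA at that visit or as that visit's contrast in the repeated-measures model;
- baseline VAS joins age, sex and disease duration as a covariate;
- the contrasts at 4 and 12 weeks after treatment are secondary;
- this model remains primary whatever the observed distribution, and the rank test is a sensitivity analysis.

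The cost is analysis wording only. VAS is already collected at every visit needed, and neither the sample size nor the schedule changes. The wording should be settled before unblinding.

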#### Inclusion criteria

Participants who match the inclusion criteria will be included: (1) patients with NP as the main complaint and a visual analog scale (VAS) score of pain severity exceeding 4 points but less than 10 points (range 0–10 points), (2) for a duration of ≤ 3 months, (3) aged 18–60 years, and (4) agreeing to sign informed consent.

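### The efficacy ANCOVA omits the baseline value of the outcome from its covariates: a valid analysis, but generally less precise than it could be at no cost

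*Protocol article*

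**What the plan says.** - Outcomes section: "The primary outcome is the change of VAS scores at baseline and after the end of treatment".
- Clinical data analysis section: groups are compared by a repeated measures ANCOVA, "taking into account the baseline values of age, sex and disease duration as covariates". No other section adds the baseline value of the outcome to the model.
- Same section, on baseline comparability: "test and chi-square test will be used to compare the differences between groups at baseline". No adjustment is tied to the result of these tests.
- Inclusion criteria: a VAS "score of pain severity exceeding 4 points but less than 10 points", so starting pain can differ appreciably between patients.
- Randomization section: 1:1 allocation, with no stratification by VAS described.
- Table 1: VAS and ROM are recorded at weeks 0 and 2. NDI, PPT, SF-36, SAS and SDS are recorded at week 2. All of these precede treatment.

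**The concern.** The pre-treatment value of a score is usually among the best available predictors of its later value, and here it is the obvious covariate left out of a list that the article states explicitly. A reader who followed the text would fit the model without it.

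Two things are at stake. The first is precision. A change score fixes the coefficient on baseline at 1, whereas ANCOVA estimates it, and unless the true slope is 1 the change score carries avoidable variance. The second is how a chance baseline difference is handled. If the true slope is below 1, subtraction over-corrects and flatters the arm that starts with more pain; if it is above 1, it under-corrects. Entering baseline as one level of the repeated factor does not help, because the group-by-time contrast between baseline and end of treatment is then the same change-score contrast. A group main effect would be worse, since it would average in a visit before any treatment was given.

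If baseline VAS were added only after an imbalance had been seen, the choice would be data-driven. That is the reason to fix it now.

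**Working it through.** **Inputs from the article (Sample size section).** Group A: "the average reduction of VAS score in group A was 2.86±0.99". Group B: "the average reduction of VAS score in group B was 2.14±0.99". Difference 2.86 − 2.14 = 0.72; SD of the change 0.99; two-sided alpha 0.05; target power 80%; 34 per group before dropout and 43 after.

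**Inputs not in the article (assumed).** Pre-post correlation ρ from 0.3 to 0.7. Ratio k = baseline SD / post-treatment SD, set to 1 and then to 0.6–0.8. The lower ratios are considered because entry limits VAS at baseline, while no such limit applies after treatment.

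**The plan's own figure.** n = 2 × 0.99² × (1.960 + 0.842)² / 0.72² = 29.7, so 30 per group and not the stated 34. The same formula gives 34 with power 0.85 (33.9). The dropout step is consistent with 34: 34 / 0.8 = 42.5, so 43. This is a separate matter and errs on the safe side; 34 and 43 are used below as stated.

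**Power as the plan stands.** Two-sample t-test, difference 0.72, SD 0.99: 84.0% at 34 per group and 91.5% at 43.

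**Variance with the baseline covariate.** With s₁ the baseline SD and s₂ the post-treatment SD:

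- change score: s₁² + s₂² − 2ρs₁s₂
- ANCOVA: s₂²(1 − ρ²)
- difference: (s₁ − ρs₂)², never negative, and zero only when the slope ρs₂/s₁ is 1
- ratio, ANCOVA to change score: (1 − ρ²) / (1 + k² − 2ρk), which is (1 + ρ)/2 when k = 1

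Example, k = 0.8 and ρ = 0.3: 0.91 / (1 + 0.64 − 0.48) = 0.91 / 1.16 = 0.78.

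| k | ρ = 0.3 | ρ = 0.5 | ρ = 0.7 |
|---|---|---|---|
| 1.0 | 0.65 | 0.75 | 0.85 |
| 0.8 | 0.78 | 0.89 | 0.98 |
| 0.7 | 0.85 | 0.95 | 1.00 |
| 0.6 | 0.91 | 0.99 | 0.98 |

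**Power at 34 per group with the covariate**, using SD = 0.99 × √ratio and neglecting the degree of freedom spent:

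| k | ρ = 0.3 | ρ = 0.5 | ρ = 0.7 |
|---|---|---|---|
| 1.0 | 95.6% | 92.7% | 89.3% |
| 0.8 | 91.6% | 87.8% | 84.7% |
| 0.7 | 89.3% | 85.8% | 84.0% |
| 0.6 | 87.2% | 84.5% | 84.7% |

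At 43 per group with k = 1, power rises from 91.5% to 98.5%, 97.1% and 95.1%.

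**Chance imbalance.** A baseline difference of one standard error, s₁√(2/n), moves the change-score contrast relative to the ANCOVA contrast by |s₁ − ρs₂| × √(2/n) = 0.99 × √(1 − ratio) × √(2/n). At 34 per group, √(2/34) = 0.243.

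- k = 1: 0.14, 0.12 and 0.09 points for ρ = 0.3, 0.5 and 0.7. The middle figure is 0.12 / 0.72 = 17% of the target difference.
- k = 0.8: 0.11, 0.08 and 0.03 points.
- k = 0.7, ρ = 0.7: no shift, because the slope is 1.

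**The case against.** - **Bias.** A reader might infer that the primary estimate is biased. The document does not support that. Allocation is randomised 1:1, so the change-score contrast is unbiased over randomisation. What remains is an effect conditional on the imbalance that happens to occur.
- **Baseline is not ignored.** It enters by subtraction, and perhaps also as a level of the repeated factor; the article does not say which. This stands as a defence of validity. It does not meet the efficiency point, because both routes fix the slope at 1.
- **Size.** A reader might take a gain of 15% to 35% as established. That range needs equal SDs before and after treatment, and the VAS limits at entry make a smaller baseline SD plausible. With k between 0.6 and 0.8 the gain is about 22% down to nothing. The claim that subtraction over-corrects likewise holds only when the slope is below 1.
- **Power.** A reader might infer an underpowered trial. On the article's own inputs power is 84% at 34 per group, above the 80% target. The full analysis set is primary and missing values are carried forward, so the analysed number may be nearer 43, where power is 91.5%.
- **Wording.** Speaking of a baseline value of sex is odd, and a comma may have been lost after *baseline values*. That is possible, but the text as printed does not include baseline VAS and would need correcting either way.

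**Conclusion.** The point holds as one of efficiency and prespecification. The stated covariates leave out the baseline value of the outcome, nothing else in the article supplies it, and the measurement is already scheduled. The analysis as written is valid. Adding the covariate cannot raise the residual variance, apart from the one degree of freedom, and under the assumptions examined lowers it by between about 0% and 35%. Power at 34 per group would move from 84% to at most about 96%.

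These figures rest on the pilot difference and SD, on assumed correlations of 0.3 to 0.7 and on assumed SD ratios of 0.6 to 1. They also take the change SD of 0.99 as the starting residual SD, so any part of the gain already absorbed by the three listed covariates is not deducted; the article gives no basis for estimating it.

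This should be fixed because it is a free improvement to the primary comparison. Leaving it as it is would not invalidate the trial.

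**What to change.** For the primary outcome, state the covariates as: baseline VAS (week 2, before treatment), age, sex, and duration of disease. For NDI, PPT, ROM, SF-36, SAS and SDS, replace baseline VAS with the matching pre-treatment score. Say that the repeated factor contains post-baseline visits only, and that the end-of-treatment group contrast from this model is the primary comparison. Naming week 2 also settles which of the two pre-treatment VAS readings is used.

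The cost is one phrase in the analysis section and one degree of freedom per model. No new data, visits or patients are needed. The change should be made before treatment groups are compared.
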